### 2.5. Sample size estimation

Sample size estimation was performed by G.power3.1. Statistical efficacy analysis was performed based on a previous study.^[14]^ A two-sided test was selected, α was set to 0.05, Statistical power was set to 0.8, and the sample size estimation resulted in 34 participants. Considering a 20% dropout rate, the finalized sample size was 40 individuals.

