### 2.6. Randomization, concealment, and blinding

A random sequence will be generated by SPSS 22.0, and patients will be randomly assigned to experimental and control groups based on a 1:1 ratio. The randomization grouping results will be stored in opaque, sealed envelopes with serial numbers marked on the cover. These envelopes were opened only before the official start of the intervention.

Blinding of therapists and patients is not possible due to the limitations of the intervention method. Data collection was performed and recorded by specialized personnel, and data analysis was performed by an independent statistician. The grouping of patients was not known for the above population.

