### 2.8. Outcome measures

The patients were tested for outcome measures before and at the end of treatment.

(1)Pain

The patient’s low back pain level is assessed by the visual analogue scale.^[16]^ The score ranges from 0 to 10, with higher scores indicating greater pain.

(2)Muscle strength

Muscle strength is evaluated by grip strength of both upper limbs and isometric muscle strength of the trunk, hip and knee joints. Grip strength is assessed by an electronic grip strength meter. Isometric strength of the trunk and knee is evaluated by the Biodex system with a centripetal contraction mode. The test speeds are slow contraction (60°/s) and fast contraction (180°/s), and the test types are flexion and extension. The test sites were the left and right sides of the body, with no right or left side of the trunk. The outcomes include peak torque, average peak torque, average power, and peak flexor-to-extensor torque ratio.

(3)Balance

The static balance test will be conducted by the Italian Tecnobody balance system. Patients will stand with their right foot in the center of the pressure platform, then bend their left knee backward by 90° while crossing their hands at the waist, and tried to maintain standing with eyes open and eyes closed for 30 seconds each, with 15 seconds rest between groups. Static balance outcomes include the distance of plantar center of gravity pressure movement (mm), the area of movement trajectory (mm^2^), the deviation of the center of gravity in the X-axis and Y-axis (mm), and the average movement speed in the anterior-posterior and left-right directions (mm/s).

(4)Bone mineral density

BMD will be measured by Dual-energy X-ray absorptiometry at lumbar spine 2-4(L_2-4_) and femoral neck.

(5)Bone metabolism

After fasting for more than 12 hours, 10 mL of blood will be drawn from elbow vein in the morning of the next day, and serum bone metabolism indexes will be measured using a fully automated enzyme-labeled immunoassay instrument. The serum bone metabolism indexes include parathyroid hormone, osteocalcin, 25-hydroxyvitamin D3 (1,25(OH) 2D3), type I procollagen aminoterminal peptide and type I collagen carboxy-terminal peptide.

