### 2.9. Statistical analysis

Statistical analysis will be performed by SPSS 22.0. If the data conforms to the normal distribution, paired *t* test is used for intra-group comparison and an independent-sample *t* test for inter-group comparison; a non-parametric test is conducted when the data does not conform to normal distribution. Differences are considered statistically significant at *P* < .05.

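### No primary outcome is named and five outcome families are each judged at P < .05, so an efficacy claim on any one variable is not prevented, and the stated power is tied to no outcome named in the text

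*Protocol article*

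**What the plan says.** The abstract and section 2.8 of the protocol article list five outcome families side by side: pain, muscle strength, balance, BMD and bone metabolism. Neither place calls any of them primary or secondary.

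Most families contain several variables. For the Biodex tests, section 2.8 says "The outcomes include peak torque, average peak torque, average power, and peak flexor-to-extensor torque ratio", at two speeds, in flexion and extension, and on both sides except for the trunk. Balance has six measures with eyes open and with eyes closed.

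Section 2.9 prescribes paired tests within groups and independent-sample tests between groups (non-parametric if the data are not normal). It gives one threshold for all of them: "Differences are considered statistically significant at" P < .05.

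On sample size, section 2.5 says: "Statistical efficacy analysis was performed based on a previous study". It continues "A two-sided test was selected, α was set to 0.05" and "Statistical power was set to 0.8, and the sample size estimation resulted in 34 participants". It gives no outcome, effect size or standard deviation.

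The Discussion says that a comprehensive evaluation across these domains is able to show that the programme works and will inform clinicians' choice of exercise programme.

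**The concern.** A confirmatory trial needs to say beforehand which comparison answers its question. Here several dozen comparisons share one unadjusted threshold, and nothing says which of them, or how many, must be significant before the programme is called effective. The authors could therefore choose the headline result after seeing the data. The 5% error rate would hold for each test taken alone, but not for the conclusion of the trial.

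The power statement has the same gap. A reader cannot tell for which of the listed variables 34 participants are enough.

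**Working it through.** **1. Number of between-arm variables** (factors from section 2.8, fully crossed)

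| Family | Calculation | Variables |
|---|---|---|
| Pain | one scale | 1 |
| Grip strength | left, right | 2 |
| Biodex, trunk | 2 speeds × (3 measures × 2 directions + 1 ratio) | 14 |
| Biodex, knee | 2 sides × 14 | 28 |
| Balance | 6 measures × 2 eye conditions | 12 |
| BMD | lumbar spine, femoral neck | 2 |
| Bone markers | five serum indexes | 5 |
| Total | | 64 |

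The hip is named as a strength site but left out of the Biodex sentence. Tested like the knee, it adds 28, giving 92. Averaging left and right for grip and knee instead gives 64 − 1 − 14 = 49. The within-group paired tests, two per variable (2 × 64 = 128), fall under the same threshold and are not counted here.

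**2. Expected false positives if the exercise has no effect**

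64 × 0.05 = 3.2, and 92 × 0.05 = 4.6. These expectations do not depend on correlation.

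**3. Chance of at least one false positive**

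Under independence the formula is 1 − 0.95^m:
- m = 64: 1 − 0.95^64 = 0.962
- m = 92: 1 − 0.95^92 = 0.991
- m = 5 (one variable per family): 1 − 0.95^5 = 0.226

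The documents give no correlations, so the values below are assumptions. The results are from simulation with normal test statistics and 64 tests.

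| Assumed correlation | 0.5 | 0.7 | 0.8 | 0.9 |
|---|---|---|---|---|
| Same correlation between all 64 | 68% | 44% | 32% | 20% |
| Five independent families (1, 44, 12, 2, 5 variables), correlation within family only | about 80% | 65% | about 55% | about 45% |

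**4. What 34 participants imply**

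The plan's 34 cannot be reproduced, because no effect size is given. It can only be inverted. Allocation is 1:1 (section 2.6), so there are 17 per arm. With two-sided alpha 0.05 and power 0.80:
- normal approximation: d = (1.960 + 0.842) × √(2/17) = 0.96
- t test (noncentral t): d = 0.99

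The calculation thus assumes a difference of about one standard deviation on a variable that the text does not name.

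**5. Why adjusting across all the tests is not the way out**

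Bonferroni over 64 tests uses 0.05/64 = 0.00078 per test. At d = 0.99 and 17 per arm, power per test falls from 80% to about 24%. Over five key variables the level is 0.05/5 = 0.01 and the power is about 56%.

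**The case against.** Several objections carry weight.

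- **Threshold, not decision rule.** A reader might infer that section 2.9 lets any single significant variable count as success, or that it declares every comparison significant. It does neither. It sets a per-comparison level, and no section says how results combine. What stands is that no success criterion is fixed, so a claim on any one variable is not ruled out. The probabilities in step 3 describe that possible use.
- **Correlation.** A reader might also infer that a false positive is likely. The figures do not secure that. Of the 64 variables, 42 are Biodex outputs, many from the same muscle tests, and high correlation among them is plausible. At a common correlation of 0.7 or more, the chance is below one half.
- **The count.** Section 2.8 lists factors but does not say that each combination is analysed separately. Sixty-four is the full crossing without the hip, not a proven minimum.
- **The cited study.** The study behind section 2.5 may well fix an outcome. The text supports only that none is named here, not that the calculation had none.
- **Material elsewhere.** A multiplicity procedure is commonly left to an analysis plan, and its absence is not the point. The primary outcome and the outcome behind the sample size are different: they define the trial and belong in the protocol. The threshold in section 2.9 is also a stated rule, not a silence.

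**Conclusion.** The point holds in this form. The protocol names no primary outcome, judges five equal families at P < .05 without a hierarchy, and states that the evaluation can demonstrate efficacy. Under no effect, about 3.2 of 64 between-arm tests would be significant. The chance of at least one is well above the nominal 5% in every case examined, from about 20% to 96%. That range rests on assumed correlations and on the full-crossing count. One variable per family, if independent, already gives 23%.

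The 80% power refers to no outcome or effect size named in the text. It holds only where the standardised difference is about 0.99, taking a two-sample t test with 17 per arm.

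This should be fixed, because the efficacy claim in the Discussion depends on it.

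**What to change.** Make a dated amendment before anyone looks at outcome data by arm, with a matching registry entry if one is needed:

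1. Name one primary outcome, at one site, side or condition, at 24 weeks, compared between arms at two-sided 0.05. Use the outcome behind the 34-participant calculation if it is among those listed; otherwise choose one and restate the power for it.
2. State in section 2.5 the outcome and effect size that the power refers to.
3. Label all other outcomes secondary or exploratory, and report estimates with 95% confidence intervals.
4. If one key variable per family must carry a claim, name the five and apply Holm across them.

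No extra data are needed. The sponsor gives up the freedom to claim efficacy on whichever variable turns out significant. Section 2.1 says the study started in November 2022, and patients and therapists are not blinded, so the amendment must be justified and must record that no outcome data by arm had been seen.

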### 2.10. Data management and monitoring

Electronic data collected will be stored in encrypted spreadsheets, and paper data will be kept in a file cabinet and guarded. In addition, the patient’s signed informed consent form and the original case notes will be stored in the file cabinet. A data monitoring committee, independent of the investigator, will be established to review the quality and integrity of the data at regular intervals (1 month).

## 3. Discussion

With the increasing trend of population aging, the elderly are vulnerable to POP and has become a global public health problem.^[17]^ Among them, the incidence of osteoporotic fractures exceeds 40%, which can lead to pain, depression, loss of functional independence, decreased quality of life, and increased economic burden and mortality after fracture.^[18]^ In recent years, the ability of exercise to prevent the occurrence of POP in the elderly has been confirmed by scholars.^[19]^ However, most of the exercise prescriptions developed in previous studies have certain limitations: they are not personalized and quantified, which may not only lead to failure to achieve the expected efficacy, but also may even cause secondary injury; the interventions are in a single form, which may easily lead to poor patient compliance. Therefore, we developed a personalized exercise prescription for patients with POP. The program is based on the traditional Chinese exercise -Yi Jin Jing, and combines aerobic exercise and strength training to make patients actively complete exercise training through multi-modal exercise types. In order to ensure the exercise intensity of the patient, we equipped the patient with a Polar heart rate belt to enable the patient to complete the exercise program within the target heart rate range.

In addition, previous studies have tended to focus on skeletal health, while other physical functions of patients with POP have been neglected. Therefore, in order to systematically evaluate the efficacy of the exercise prescription of this protocol in patients with POP, we not only measured BMD and serum bone metabolism indexes but also observed changes in pain, muscle strength and balance. A comprehensive evaluation can effectively demonstrate the efficacy of this program and provide an evidence-based basis for clinicians to select an exercise program.

This study also has some limitations. First, due to the intervention modality, this study could not be blinded to therapists and patients. Second, due to sample size and single-center limitations, the results of this study may have potential bias.

Overall, this study will optimize a new personalized exercise prescription for improving POP and provide new insights for clinical practice.
